### Participation timeline

2.9

**Baseline (day 0)**oObtain and document consent from participant on study consent form.oVerify inclusion/exclusion criteria.oObtain demographic information, medical history, medication history, alcohol and tobacco use history.oRecord results of physical examinations and 12-lead ECG.oCollect blood specimens (complete blood count, biochemistry and inflammatory biomarkers).oImaging procedures: transthoracic 2-D echocardiography, late gadolinium-enhancement CMRoCatheter ablation (radiofrequency or cryoablation)**Follow-up visits (month 1,3,6)**oRecord results of physical examinations, 12-lead ECG and medical history.oImaging procedures: transthoracic 2-D echocardiography**Final study visit (month 12)**oRecord results of physical examinations, medical history,12-lead ECG and determination of serum levels of inflammatory biomarkers and NT-proBNPoImaging procedures: transthoracic 2-D echocardiographyoEnd-point evaluation.

### Study procedures

2.10

Medical history, clinical examination, laboratory tests (complete blood count, biochemistry, serum level of hsCRP, MMP, IL6 and NT-pro-BNP);12-lead ECG2D transthoracic echocardiography with measurement of: cardiac diameters, volumes, valvular function and regurgitation, pressure gradients, left ventricular systolic and diastolic function and ejection fraction.Late Gadolinium-Enhancement CMR with the evaluation of: left and right atrial volume, volume of epicardial adipose tissue, degree of atrial and ventricular fibrosisPulmonary vein isolation radiofrequency ablation with advanced 3D mapping system or cryoablation.

### Data collection

2.11

All the information will be collected in a database that consists of patient's background, medical history, medication, imaging features provided by cardiac ultrasound, CMR and imaging post-processing.

### Sample size

2.12

The study will include 100 subjects with AF undergoing successful ablation of pulmonary veins via interventional route. After analysis of follow-up data, patients will be distributed in two groups according to the presence or absence of recurrent episodes of AF during the follow-up.

Sample size calculation was performed using the StatMate 2.0 software. For sample calculation, the proportion of event-free population was estimated at 60%. According to this calculation, a sample size of 50 patients in each subgroup has a 90% power to detect an increase in MACE-free rates proportion of 0.29, with a significance level (alpha) of 0.05 (2-tailed). Therefore, the total sample size was established at 100 patients.

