## Abstract

**Introduction::**

Interventional ablation has been demonstrated to represent an effective therapy in patients with atrial fibrillation (AF), leading to restoration and maintenance of sinus rhythm in the majority of cases. However, recurrence of AF is encountered in 35% to 40% of cases, and the causes for this frequent complication have not been elucidated so far.

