### Outcomes

2.8

The *primary outcome* of the study is represented by the rate of AF recurrence at 1-year post ablation, documented by either ECG or Holter monitoring.

*Secondary outcome* refers to rate of re-hospitalization, rate of survival without relapse and rate of major adverse cardiovascular events (MACE rate, including cardiovascular death or stroke)

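### The only power statement compares MACE-free rates between groups formed by AF recurrence, so the sample of 100 has no stated justification for the primary question

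*Protocol article*

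**What the plan says.** - **Calculation (2.12 Sample size).** The reference rate is given as "the proportion of event-free population was estimated at 60" per cent, without naming the event. The result is "a sample size of 50 patients in each subgroup has a 90% power to detect an increase in MACE-free rates proportion of 0.29". The test is two-sided at the 5% level. The total of 100 is derived from this alone.
- **Subgroups (2.3, 2.5 and 2.12).** The two groups are patients whose AF recurs and patients whose AF does not. Membership is known only after follow-up.
- **Outcomes (2.8).** The primary outcome is the "rate of AF recurrence at 1-year post ablation, documented by either ECG or Holter monitoring". The "rate of major adverse cardiovascular events (MACE rate, including cardiovascular death or stroke") is listed among the secondary outcomes.
- **Primary objective (1.2).** It concerns the association of left atrial and left ventricular fibrosis on CMR, and of inflammatory biomarkers, with recurrence after ablation.
- **Expected recurrence (Abstract, Introduction).** "recurrence of AF is encountered in 35% to 40% of cases".
- **Tests (2.13).** t test or Mann-Whitney for continuous variables, Fisher's exact test for categorical ones.

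**The concern.** The sample size section answers a question that the study does not put first. It takes the primary outcome as the grouping variable and a secondary outcome as the response. The exposures of interest, fibrosis and biomarkers, do not appear.

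The 60% figure looks like an AF-free rate, because it is one minus the upper end of the quoted recurrence range, yet the effect is labelled MACE-free. Equal groups of 50 are assumed although nobody controls how many patients fall into each group.

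At stake is how the result will be read. The Discussion and Conclusions say the study will validate predictors of recurrence. A reader who sees 90% power will assume that it refers to those predictors. If fibrosis shows no difference, the article gives no planned marker effect against which to judge whether the study could have seen one.

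**Working it through.** **Inputs from the article.** Two-sided alpha 0.05; reference proportion p1 = 0.60; increase 0.29, so p2 = 0.89; 50 per group; recurrence 35–40%; Fisher's exact test and t test as planned analyses. The article gives no MACE rate and no marker mean, SD or target difference.

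**Step 1. Reproduce the stated power.** The normal approximation, with mean proportion p̄ = (0.60 + 0.89)/2 = 0.745 and n = 50, is

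power = Φ{ [0.29 − 1.96·√(2·p̄(1−p̄)/n)] / √[(p1(1−p1) + p2(1−p2))/n] }

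- √(2 × 0.745 × 0.255/50) = 0.0872
- √((0.2400 + 0.0979)/50) = 0.0822
- (0.29 − 1.96 × 0.0872)/0.0822 = 1.45, so power = 92.6%
- With continuity correction (0.29 less 1/50): 88.6%
- Fisher's exact test by full enumeration: **90.2%**

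The stated 90% is correct for its inputs.

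**Step 2. Ask what is being compared.** There are two readings of the event.

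- *Literal MACE.* A 60% event-free rate means 40% MACE in one of the two groups. With 11% in the other group and equal sizes, the overall rate is (0.40 + 0.11)/2 = 25.5%. Nothing in the article supports either figure. An increase of 0.29 is possible only if the worse group's MACE-free rate is at most 1 − 0.29 = 0.71.
- *MACE-free as a slip for AF-free.* The match with 35–40% recurrence makes this plausible. But the groups are defined by recurrence, so the AF-free proportion is 0% in one and 100% in the other by construction, and there is nothing to test. Two equal groups defined by a marker would make the comparison meaningful, but the article describes none. Even then, with 60% AF-free overall and a difference of 0.29 (0.745 versus 0.455), 50 per group gives 85% by normal approximation and 81% by Fisher, and 90% needs 58 per group by normal approximation.

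Neither reading yields a power statement for the primary objective.

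**Step 3. Check the equal split.** At 35–40% recurrence, 100 patients divide into about 35–40 and 60–65. The binomial probability of 50 or more recurrences in 100 is 2.7% at a 40% rate and 0.15% at 35%. The effect on power for 0.60 versus 0.89 is small:

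| Split | Fisher power (range over which group has 0.60) |
|---|---|
| 50/50 | 90.2% |
| 40/60 | 90.3–90.9% |
| 35/65 | 88.8–89.3% |

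**Step 4. What 100 patients give for the primary objective.** Take a continuous baseline marker compared between recurrence groups by two-sided 5% t test. To first order the detectable standardised difference is d = (1.960 + z)·√(1/n1 + 1/n2), with z = 1.282 for 90% power and 0.842 for 80%. For 40/60 at 90% this is 3.242 × √(1/40 + 1/60) = 3.242 × 0.2041 = 0.66. The noncentral t distribution adds slightly:

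| Split | d at 90%: normal / t | d at 80%: normal / t |
|---|---|---|
| 40/60 | 0.66 / 0.67 | 0.57 / 0.58 |
| 35/65 | 0.68 / 0.69 | 0.59 / 0.59 |

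For an assumed difference of 0.5 SD, the normal approximation gives 69% power at 40/60 and 67% at 35/65.

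**The case against.** The strongest reply is that the stated sum is right, the total would not change, and MACE-free may be a slip of wording. The first two parts stand: this is not an arithmetic error, and no larger sample is called for here. The third does not rescue the paragraph, because an AF-free rate cannot be compared between groups defined by AF recurrence.

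The equal split can also be defended in part. Section 1.1 quotes success of 70% in paroxysmal and 50% in persistent AF, so a cohort made up wholly of persistent AF could approach 50/50. It costs little power in any case. It is a supporting inconsistency and not the main defect.

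It is fair, too, that the 40% MACE figure is inferred, because the sentence giving 60% does not name its event. A reader might infer that the plan expects 40% of all patients to suffer cardiovascular death or stroke. The article does not say so: even on the literal reading, 40% applies to one group only, and the MACE definition is worded as including those two events, which need not be a complete list.

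Finally, estimates and confidence intervals would still make a null marker result interpretable to a degree. That is true. What is missing is a planned effect to set them against, while a 90% figure invites the reader to think that one exists.

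A condensed article may leave detail to a fuller document. Here, however, a calculation is stated, and it conflicts with the article's own outcomes, objective and grouping.

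**Conclusion.** The point holds as a mismatch of endpoint and design. The sole justification for 100 patients powers a secondary outcome between groups formed by the primary outcome, and says nothing about detecting a link between fibrosis or biomarkers and recurrence.

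In size, 100 patients at 35–40% recurrence give 90% power for a marker difference of 0.67–0.69 SD and 80% power for 0.58–0.59 SD. This assumes an approximately normal marker, all 100 patients evaluable, one marker tested at 5% without adjustment, and the quoted recurrence range. At 30% recurrence the 90% value would be about 0.71 by normal approximation.

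Two stronger conclusions are tempting and not supported. One is that 100 patients are too few: the article gives no target marker difference, so adequacy cannot be judged either way. The other is that the MACE comparison has some particular low power: the article gives no MACE rate, so only the absence of support for 60% versus 89% can be asserted.

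**What to change.** Keep 100 patients. In section 2.12, delete the MACE-free power claim and the assumption of 50 per subgroup, and replace them with wording such as:

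> With 100 evaluable patients and 35–40% recurrence, a comparison of a continuous baseline marker (e.g. LA fibrosis) between the recurrence and no-recurrence groups by two-sided 5% t test has 90% power for a standardised difference of 0.67–0.69 and 80% power for 0.58–0.59, per marker and without multiplicity adjustment; loss to follow-up would raise these values.

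LA fibrosis is only an example here; the wording does not make it the sole primary marker. MACE can stay a secondary outcome with no power claim attached. If the investigators have a marker difference that they consider relevant, adding it would turn this description into a justification.

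The cost is one paragraph. The stated sensitivity will look less favourable than before, and no extra patients are needed.

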### Statistical analysis

2.13

Statistical analysis will be performed using Graph Pad InStat 3.10 software at the level of significance 5%. All data will be checked for normality. Continuous variables with normal distribution will be presented as mean ± standard deviation and will be compared using *t* test. Non-normally distributed variables will be analyzed using the Mann-Whitney test. Categorical variables will be expressed in numbers and percentages and will be compared using the Fisher exact test.

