### Background and rationale

1.1

Atrial fibrillation (AF) has an increasing prevalence, being currently the most frequent type of supraventricular arrhythmia and representing a significant burden for the healthcare system. In most of the cases, myocardial tissue located at the level of the pulmonary veins represents the origin of AF. The pathophysiology of AF is still incompletely understood, several studies suggesting that profibrotic and inflammatory processes can play a crucial role in the development of AF.^[1]^ So far the success rate of AF ablation is not very high, reaching 70% in patients with paroxysmal AF and 50% in cases with persistent AF. Several risk factors for the occurrence and recurrence of AF have been described in the literature, including left atrial (LA) enlargement, left ventricular (LV) dysfunction, the amount of epicardial fat surrounding cardiac structures, or myocardial fibrosis.^[2]^ However, the relationship between inflammatory-mediated myocardial fibrosis and AF recurrence after radiofrequency catheter ablation has not been elucidated so far.^[3]^

Here we present the study protocol of the FIBRO-RISK trial, a prospective, single-center, cohort study which aims to investigate the impact of inflammatory-mediated myocardial fibrosis on the risk of recurrence after successful catheter ablation of AF.

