### Study objectives

1.2

The *primary objective* of the study is to investigate the correlation between the degree of LA and LV fibrosis quantified by cardiac magnetic resonance (CMR), inflammatory biomarkers, and the risk of AF recurrence post catheter ablation.

The *secondary objective* of the study is to investigate the correlation between structural remodeling of the left and right atrium, epicardial fat tissue volume and serum inflammatory biomarkers in patients with AF undergoing successful catheter ablation and their impact on long term outcomes.

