## Discussion

3

This study presets the protocol of a prospective, single-center, cohort study which aims to investigate the impact of inflammatory-mediated myocardial fibrosis on the risk of recurrence after successful catheter ablation of AF.

Although AF ablation procedures are constantly improving, recurrences continue to be problematic as a significant proportion of patients present with AF relapse despite an optimum management in the post-ablation period.^[1,4]^ In the latest years, a large number of studies tried to identify predictors for a successful outcome on long term after AF ablation, however reliable clinical markers to predict sinus rhythm maintenance or AF recurrence have not been identified so far. The main contribution of the present study will be to validate new clinical features, such as inflammatory biomarkers, epicardial fat, ventricular remodeling or myocardial fibrosis, as predictors of AF recurrence in patients who are scheduled for catheter ablation. In this trial we hypothesize that several imaging markers associated with cardiac structural alteration, provided by CMR (such as LA, LV fibrosis, atrial volumes or the amount of epicardial fat), associated with serum inflammatory biomarkers (IL-6, MMP-9, hsCRP) could form a powerful prediction panel to predict the risk of AF recurrence in the post ablation period, reflecting the impact of inflammatory-mediated myocardial fibrosis on the risk of arrhythmia.

The relationship between inflammation, myocardial injury and atrial fibrillation has been extensively studied in the recent years.^[5]^ It is well known that a higher amount of atrial fibrotic tissue can favor atrial arrhythmogenesis.^[2,6]^ At the same time, the amount of contrast enhancement in the LA wall, considered to represent the volume of fibrotic tissue of the total LA wall, has been recently described by prospective trials to be independently associated with the likelihood of recurrent arrhythmia after ablation.^[2,6,7]^ Previous studies showed that pre-existing fibrosis on LGE-CMR was the strongest independent predictor of ablation procedure failure and arrhythmia recurrence.^[8]^ McGann et al proved that subjects with >30% atrial fibrosis on LGE images at baseline had a 71% chance of AF recurrence at 1 year.^[9]^

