Besides inflammation, neurohormonal activation, classically associated with ventricular dysfunction, has been shown to play a significant role in the recurrence of AF following pulmonary vein isolation.^[20,21,23–26]^ A very recent study demonstrated that in patients admitted in an intensive care facility, the presence of ventricular remodeling leading to ventricular dysfunction was associated with a higher incidence of AF and conduction abnormalities.^[27]^ NT-proBNP is a biomarker reflecting ventricular dysfunction, which has been shown to predict AF recurrence unrelated to ablation procedure.^[28,29]^ However, it still remains unclear if these biomarkers are useful predictors of AF recurrence after ablation. In the FIBRO-RISK study, we aim to validate, for the first time in the literature, the role of ventricular remodeling, serum biomarkers associated with ventricular dysfunction, inflammation and myocardial fibrosis, assessed by LGE-CMR, as independent predictors of AF recurrence after successful catheter ablation, in order to prove that inflammation can play a significant role in the complex interrelation between myocardial dysfunction, remodeling and AF recurrence.

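### The named analyses are unadjusted two-group tests, which cannot support independent prediction of recurrence or estimate how the markers relate to one another

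*Protocol article*

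**What the plan says.** **Methods.** Section 2.13 (Statistical analysis) sets out the tests at the 5% level. For normal data: "Continuous variables with normal distribution will be presented as mean ± standard deviation and will be compared using" a t test. For other continuous data: "Non-normally distributed variables will be analyzed using the Mann-Whitney test". For categorical data: "Categorical variables will be expressed in numbers and percentages and will be compared using the Fisher exact test". Sections 2.3, 2.5 and 2.12 define one pair of groups, recurrence and no recurrence during follow-up. No regression, adjusted, correlation or discrimination method is named anywhere in the article.

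**Aims.**
- Section 1.2 (Study objectives), primary: to "investigate the correlation between the degree of LA and LV fibrosis", inflammatory biomarkers and the risk of recurrence. The secondary objective asks for the correlation between atrial remodelling, epicardial fat and inflammatory biomarkers.
- Section 3 (Discussion) repeats the aim of correlating inflammatory biomarkers with fibrosis on cardiac magnetic resonance.
- The Discussion also aims to validate ventricular remodelling, serum biomarkers and fibrosis "as independent predictors of AF recurrence after successful catheter ablation".
- It hypothesises that the imaging and serum markers "could form a powerful prediction panel to predict the risk of AF recurrence in the post ablation period".

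**Population.** The inclusion criteria admit paroxysmal and persistent AF. Section 1.1 gives ablation success as "reaching 70% in patients with paroxysmal AF and 50% in cases with persistent AF".

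**The concern.** Independence is a statement about an adjusted effect: the marker must carry information on recurrence beyond the other known factors. None of the three named tests adjusts for anything. A marker that merely travels with AF type, or with fibrosis, will tend to differ between the recurrence groups without adding information of its own.

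This matters here because the study's own hypothesis, fibrosis mediated by inflammation, presumes that the markers are correlated. Section 1.1 also lists atrial enlargement, ventricular dysfunction, epicardial fat and fibrosis together as risk factors.

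The marker-to-marker aims are a second gap. Comparing each marker by recurrence status does not estimate how two continuous markers relate to each other. If the section is followed as written, the paper could call a merely correlated biomarker an independent predictor, and the correlations that it promises would have no planned estimate.

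**Working it through.** **1. The plan's own figure.** Section 2.12 states 90% power with 50 per subgroup for an increase of 0.29 from 60% event-free, two-sided 5%. Power of the Fisher exact test is the sum, over all pairs (x, y), of Bin(x; 50, 0.60) × Bin(y; 50, 0.89) for pairs with p ≤ 0.05. The result is 0.902, so the figure reproduces. It is power for an unadjusted comparison of two proportions, not for an adjusted effect, a panel or a correlation.

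**2. Aims against methods.**

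| Aim | Needs | Named in 2.13? |
|---|---|---|
| Marker associated with recurrence | Two-group comparison | Yes |
| Marker independently predictive | Adjusted model | No |
| Inflammation with fibrosis; fat and remodelling with biomarkers | Correlation or regression between markers | No |
| Panel (hypothesis) | Joint model and a performance measure | No |

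**3. Confounding by AF type.** Recurrence is inferred by subtraction from section 1.1: 100 − 70 = 30% paroxysmal and 100 − 50 = 50% persistent. The article gives no persistent share p. Its overall recurrence of 35% to 40% (Abstract) bounds p through 0.30 + 0.20p:
- 0.35 gives p = 0.05/0.20 = 25%.
- 0.40 gives p = 0.10/0.20 = 50%.

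The simulation used 100 patients and a marker with no effect within AF type but a mean higher in persistent AF. The shifts are assumed. It shows how often the marker is significant at 5%:

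| Shift (SD) | Unadjusted, 25% persistent | Unadjusted, 50% persistent | Adjusted for AF type |
|---|---|---|---|
| 0.5 | 6.2% | 7.8% | about 5% |
| 0.8 | 9.2% | 11.7% | about 5% |
| 1.0 | 10.7% | 14.7% | about 5% |

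These used 10,000 replicates for the unadjusted columns. Repeat runs at 50% persistent gave up to 15.2% unadjusted and 4.6% to 5.2% adjusted.

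**4. Confounding by fibrosis.** The assumed model is logit P(recurrence) = −0.45 + 0.8 × fibrosis (in SD), so about 40% recur and the odds ratio is exp(0.8) = 2.2 per SD. The biomarker is ρ × fibrosis + √(1 − ρ²) × noise, with no effect of its own, in 100 patients:

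| ρ | Unadjusted t test | Logistic, adjusted for fibrosis |
|---|---|---|
| 0 | 5.3% | 5.1% |
| 0.3 | 17–18% | about 4–5% |
| 0.5 | 38–40% | about 4–5% |
| 0.7 | 69% | about 4–5% |

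Ranges are over two runs, of 1,500 and 3,000 replicates; ρ = 0 was in the first run only. Neither the 0.8 nor ρ comes from the article.

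**5. How large a model the data can carry.** Expected recurrences are 100 × 0.35 = 35 to 100 × 0.40 = 40. At an assumed 10 events per coefficient, 35/10 = 3.5 and 40/10 = 4, so 3 to 4 coefficients. The hypothesised panel has at least seven candidates (left atrial fibrosis, left ventricular fibrosis, atrial volume, epicardial fat, IL-6, MMP-9, hsCRP). That leaves 35/7 = 5.0 to 40/7 = 5.7 events per coefficient.

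**The case against.** Section 2.13 is a short paragraph in a journal article. It does not call its list exhaustive, and an unseen analysis plan could hold further models. That is fair, and the article cannot show that no adjusted model is planned. The point that remains is internal: the article fixes specific tests and states aims that those tests cannot meet, without deferring those aims to another document.

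Three stronger readings are tempting and are not supported.
- *No named method addresses the primary objective.* Too broad. Comparing fibrosis or a biomarker between recurrence groups does test its association with recurrence; with a binary outcome the pooled t test is equivalent to testing a point-biserial correlation. Only the marker-to-marker correlations lack a method.
- *The study promises a validated panel.* It does not. The panel is a hypothesis in the Discussion and appears in neither the objectives nor the outcomes. Independent prediction is also worded in the Discussion only, but as an aim.
- *Mixing radiofrequency and cryoablation biases the results.* The article gives no figure showing that recurrence differs by technique, so nothing can be concluded.

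It is also fair that the inflation from AF type alone is modest, about 1 to 10 percentage points over 5%. The larger inflation comes from correlation with fibrosis and depends wholly on assumed inputs.

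**Conclusion.** The point holds as a mismatch between stated aims and named methods. The listed tests suffice for unadjusted association of each marker with recurrence. They do not support independent prediction and do not estimate the marker-to-marker correlations; the hypothesised panel also has no method.

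The size depends on assumptions. With 25% to 50% persistent AF, recurrence of 30% and 50% inferred from the success rates, and a shift of 0.5 to 1.0 SD, false significance is about 6% to 15% unadjusted against about 5% adjusted. With a fibrosis effect of 0.8 log-odds per SD and correlations of 0.3 to 0.7, it is about 17% to 69% against about 4% to 5%. These rates show what the unadjusted tests could do; they do not forecast what this cohort will show. The mismatch itself needs none of these inputs.

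**What to change.** Add to section 2.13:
- One pre-specified logistic regression of one-year recurrence (yes/no) on left atrial fibrosis as a continuous variable and one named inflammatory marker, adjusted for AF type. That is three coefficients; allow at most one more. A yes/no outcome suits the design, because section 2.6 schedules ECGs only at months 1, 3, 6 and 12 after baseline and many recurrence times would be known only to an interval.
- The measurement time of each predictor. Section 2.3 places the biomarkers in the first 24 hours after the procedure and section 2.6.1 at baseline; these need reconciling. Imaging may fall within 7 days either side of baseline.
- Spearman correlations for inflammation with fibrosis, and for fat and remodelling with the biomarkers.
- A statement that the t, Mann-Whitney and Fisher tests are unadjusted descriptions.
- A statement that any panel is exploratory and will be internally validated.

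The alternative, at no analytic cost, is to drop the claims of independence and of a panel.

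The cost is wording, plus software able to fit a logistic model. AF type, imaging and biomarkers are already part of the planned data, so no new patients or measurements are needed. The downside is that 35 to 40 events support few covariates, so most markers will have only unadjusted results. Settle the choice before outcome data are analysed.
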